## Abstract

**Background:** The impact of a sedentary and unhealthy lifestyle on cardiovascular health is well-documented, however the current obesity and hypertension trends among children is concerning. The ExAMIN Youth SA study aims to investigate the impact of lifestyle behaviors (physical fitness/activity, dietary intake and psychosocial factors) involved in early vascular aging among South African children.

**Methods:** This study is an analytical, multidisciplinary, observational cohort study in a school-based setting. We aim to phenotype a cohort of ~1,000 primary school children (black and white boys and girls between ages 5–9 years) based on current clinical childhood conditions including hypertension and obesity. The primary phenotype is large artery stiffness and retinal microvascular diameters, both biomarkers of early vascular aging. The risk factors and mediators of early vascular aging and also responsible for the clinical conditions include physical inactivity, unhealthy diet, and life stress. Additionally, urinalysis and salivary analyses will be performed to identify biomarkers related to the pathophysiology of early vascular aging.

**Discussion:** In line with the growing prevalence of obesity and hypertension responsible for the development of early vascular aging from childhood to adulthood, this study will address the critical areas in which we observe unfavorable arterial modulation related to dietary behaviors, physical inactivity, and early life stress. Implementation of novel biological markers may further contribute to our understanding of early cardiovascular adaptations in childhood, and aid in the development of primary prevention programs.

**Trial registration:** The study was retrospectively registered on ClinicalTrials.gov on 15 August 2019 (NCT04056377).

## Background

Two of the most important future health care challenges include the global rise of hypertension and obesity. Elevated blood pressure and adiposity in childhood tracks into later life, and contribute to the burden of cardiovascular disease and type 2 diabetes (1, 2). The *Exercise, Arterial Modulation and Nutrition in Youth South Africa* (ExAMIN Youth SA) study was designed as a multidisciplinary cohort analytical study to increase our understanding of the complex mechanisms involved in the etiology of early cardiovascular alterations in a cohort of children (aged 5–9 years). This study will contribute to our understanding of the early pathophysiological changes related to unfavorable arterial modulation in childhood.

In recent years, high blood pressure and the importance of recognizing its harmful implications in children became momentous (3). However, there remains a lack of primary prevention implementation in childhood, where most impact can be made to curb early non-communicable disease onset. Many cardiovascular related complications have no early detectable clinical signs and symptoms, and may therefore go unnoticed. Hence, the potential ambivalence of not recognizing childhood hypertension (4). Elevated blood pressure and obesity are two of the modern day's most prominent risk factors for cardiovascular morbidity and mortality (5). These risk factors are becoming an even larger threat to child health, due to an increasing prevalence of unhealthy and sedentary lifestyle practices among children globally (6, 7). Worldwide analyses have indicated that the highest blood pressures are recorded in black populations (8). The vulnerable cardiovascular profile of black individuals is believed to result from a combination of factors such as rapid urbanization, physical inactivity, suboptimal dietary practices, and consequently, weight gain with an increased prevalence of childhood obesity (9).

The importance of the ExAMIN Youth SA study is the early detection of physical inactivity, unhealthy dietary behaviors and psychosocial stressors as underlying contributors of pre-clinical large- and small artery pathology—*arterial modulation*. In a previous study, we observed a high proportion (12.5%) of elevated blood pressure in black boys (aged 6–8 years), with higher arterial stiffness in all sections of the arterial tree, higher diastolic blood pressure and mean arterial pressure, a thicker carotid intima–media wall, increased total peripheral resistance and higher advanced glycosylation end-products compared to white boys of similar ages (10). Other studies also described high total peripheral resistance (11) and low socioeconomic status (12) to contribute to the burden of childhood hypertension especially among the black population. This phenotype underlined the increasing trend of early-onset vascular aging among black adult populations in South Africa.

By integrating our previous knowledge from the Arterial Stiffness in Offspring Study (also performed in children aged 6–8 years), we will further introduce urinary and salivary biomarkers that could aid in identifying early risk markers with the ability to predict potential future cardiovascular compromise due to interactions of lifestyle behaviors on arterial modulation. Among these risk markers are amino acids, acylcarnitines, and organic acids determined by novel technologies to identify metabolomic patterns known to be involved in adverse dietary behavior (13). Additionally, preliminary analyses in the Arterial Stiffness in Offspring Study yielded information of lower nitric oxide bioavailability in black compared to white boys (14), suggesting potential early signs of endothelial dysfunction. Therefore, in a larger sample in the ExAMIN Youth SA study, we aim to determine markers related to nitric oxide bioavailability such as urinary nitrite, nitrate, symmetric, and asymmetric dimethylarginines, dimethylamine, and malondialdehyde (15, 16).

In addition, we will assess the retinal vasculature in children as one of the primary outcomes. Retinal vessel diameters are valid microvascular biomarkers shown to be associated with a higher risk of hypertension and obesity, incidence of stroke and myocardial infarction as well as higher cardiovascular mortality in adults (17, 18). With elevated blood pressure not being benign in children and previously linked to target organ damage including increased carotid intima–media thickness (19) and left ventricular mass (20), this study will additionally explore the links with the retinal microvasculature as target organ damage marker in South African children. A previous study indicated that childhood obesity, high blood pressure, and physical inactivity were associated with retinal microvascular abnormalities, suggesting retinal vessel imaging as promising biomarkers for early risk stratification in children (21). No such study to date has examined retinal vessel diameters in South African children and analyzed associations with blood pressure, body composition, physical activity, and dietary or lifestyle factors. Moreover, concomitant assessment of large artery stiffness and retinal microvascular diameters allows for investigation of the cross-talk between the macro- and microcirculation. In a collaborative effort, this ExAMIN Youth SA study is aligned with the Exercise and Arterial Modulation in Children study from Basel, Switzerland (22), to allow cross-comparisons among two international cohorts, ethnicities and sex. Studies suggested that increased estrone levels in men are indicative of future diabetes risk (23) and associated with adverse lipid profiles and is apparent early in life prior to cardiovascular disease manifestations (24). However, studies in children are lacking in this regard. To establish the potential early differences and involvement of sex hormones in arterial modulation, estrone (one of the three most prominent estrogens) derived from peripheral tissue conversion in prepubertal children is of interest to investigate, especially due to its role in vascular reactivity and function as an anti-atherosclerotic agent (25).

Besides the abovementioned factors, psychosocial stress is considered to play a significant role in the development of cardiovascular disease (26). Psychosocial stress may have an impact on an individual's psychobiological processes (hypothalamic-pituitary-adrenal function, sympathetic nervous system function, endothelial dysfunction, inflammation, and autonomic control). Furthermore, researchers hypothesized that psychosocial stress might have a negative impact on health behaviors such as decreased motivation to be physically active (27). Stressful life events were found to have a negative association with self-reported health among children as well as older individuals who exercised infrequently (28). The majority of previous studies indicated that regular physical activity and improved aerobic functioning can potentially protect an individual against health risks associated with a higher perception of psychosocial stress (29). The hypothalamic-pituitary adrenal axis responses can be studied as indexed by cortisol reactivity to stressful experiences (30). The ExAMIN Youth SA study will employ a physical activity intervention in order to determine the beneficial effects of physical activity on HPA axis reactivity. Poor health and performance related fitness at a young age can negatively impact physical activity behaviors which can in turn influence cardiovascular health (31). Nevertheless, previous studies focused mostly on older children and adolescents while research investigating younger children (<8 years) is still lacking. By studying baseline cortisol levels and identifying those with higher hypothalamic-pituitary adrenal axis responses may aid in the implementation of future prevention strategies to curb early onset distress known to impact on cardiovascular health (32).

This study will implement state-of-the-art techniques and biochemical technologies to address especially behavioral contributors to hypertension and obesity development; and to subsequently provide a backdrop for school-based primary prevention interventions in South Africa.

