### Study Design

The ExAMIN Youth SA study is an analytical, multidisciplinary, observational cohort study, designed to investigate the interplay between body composition, dietary intake, physical fitness, and physical activity, psychosocial stress, cardiovascular function as well as urinary and salivary biomarkers in 1,065 children (age 5–9 years) attending public primary schools in the North West province, South Africa. The study will obtain unique high-quality data at baseline and will expand the investigations after a 4-year follow-up period to identify exposures and early vascular changes that may contribute to cardiovascular disease development in children. An outline of the study design and procedures during the baseline phases are illustrated in Figure 1.

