### Physical Fitness

Prior to physical fitness tests, the children will perform a standardized 5-min warm-up. The test battery consists of a 20 m shuttle run (endurance), a 20-meter speed test (running speed), jumping sideward (coordination and agility), standing broad jump (strength), balancing backwards (balance), jumping, catching, kicking, and running (motor skill competences and coordination). All the tests will be performed during school time in the morning at the school with the same standardized equipment.

The following physical fitness tests are included:

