#### Salivary Sampling and Analysis

On the day of participation in physical fitness assessments, each participant will be asked to provide a fasting saliva sample in provided SaliCaps (IBL International GmBH), before 8 am. Two additional saliva samples will be collected; one before the 20 m shuttle run test and another 30 min after the shuttle run intervention. This is done for a hypothalamic-pituitary adrenal axis reactivity intervention on cortisol levels, known to be involved in the harmful effects of stress exposures on cardiovascular function and biological aging (60). We will determine the salivary cortisol and estrone levels using solid phase enzyme-linked immunosorbent assays (ELISA) with the Synergy HT microplate reader, BioTek.

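### One shuttle run with saliva before and after cannot show that physical activity benefits cortisol reactivity, as the Background promises

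*Protocol article*

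**What the plan says.** The Background states that the study "will employ a physical activity intervention in order to determine the beneficial effects of physical activity on HPA axis reactivity". The reasoning just before that sentence is about regular activity and better aerobic function as protection against stress-related health risk.

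The Methods carry this out in Salivary Sampling and Analysis. On the fitness-test day "each participant will be asked to provide a fasting saliva sample in provided SaliCaps (IBL International GmBH), before 8 am". Then: "Two additional saliva samples will be collected; one before the 20 m shuttle run test and another 30 min after the shuttle run intervention". The purpose given is: "This is done for a hypothalamic-pituitary adrenal axis reactivity intervention on cortisol levels". There are thus three samples per child, two of which bracket the run.

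Physical Fitness fixes the time of day: "All the tests will be performed during school time in the morning at the school with the same standardized equipment". It describes the shuttle run as a test that continues, with speed rising every minute, until the child fails or stops, with encouragement to maximal effort.

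Study Design says: "The ExAMIN Youth SA study is an analytical, multidisciplinary, observational cohort study". The abstract says the same. No resting group, no-run day, crossover or allocation is described.

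**The concern.** The stated purpose is causal and presumes its direction: physical activity is the cause and a benefit is what will be determined. The procedure is a single bout that each child performs, with no unexercised comparison. Two things go wrong.

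- **No counterfactual.** Cortisol may change over the morning for reasons unrelated to the run. The before/after difference cannot separate that from the response to exercise.
- **Wrong exposure.** The rationale concerns habitual activity and fitness. A single maximal test provokes a cortisol response. It does not vary how active the child is.

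The risk is that a mean change after the run is read as an effect, or a benefit, of physical activity. The word intervention, used in both the Background and the Methods, invites that reading and sits badly with the observational label.

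**Working it through.** **Is there a figure to reproduce?** Not for cortisol. The only power statement (Sample Size Calculation) is 95.3% for multiple regression on blood pressure, pulse wave velocity or arteriolar-to-venular ratio. With the noncentral F test of R² on 10 predictors, f² = 0.025, two-sided 5% and λ = f² × N, power is 96.6% at N = 1,065 and 95.35% at N = 1,000. The stated figure is reproduced closely enough, but it has no bearing on the saliva component.

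**What the pre/post change contains.** Write it as

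post − pre = (response to the run) + (time-of-day change between the samples) + error.

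Every child runs, so the first two terms have no separate source of information in the mean. The fasting sample before 8 am gives a rough slope up to the run. To use it as a control, one must assume that the slope continues unchanged past the run, which nothing in the design can check. The article gives no clock time for the run.

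**Would a resting comparison rescue the claim?** Only in part. It would identify the acute response to one run. It would not show a benefit of physical activity: a rise could be read as a healthy response or as strain, and a fall as recovery or as drift. This step needs no outside physiology.

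**Dose.** One stage is about one minute, and the test ends when the child fails. Fitter children therefore do more exercise. With the last sample timed at 30 min after the run, they also have a somewhat longer interval between the two samples. Stages completed thus stand for both exercise dose and fitness.

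**Illustration of scale (all inputs assumed).** Take n = 1,000 children with both samples, no exercise effect, and a time-of-day drift of d standard deviations of the paired difference. Then z ≈ d × √1000 = 31.6 × d, and the chance of a significant two-sided 5% paired test (noncentral t) is:

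| d | z | Probability of significance |
|---|---|---|
| 0.05 | 1.6 | 35% |
| 0.1 | 3.2 | 88% |
| 0.2 | 6.3 | >99.9% |

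The same on a log scale: with an assumed SD of log change of 0.5, SE = 0.5/√1000 = 0.0158. An assumed fall of 4% gives ln(0.96)/0.0158 = −0.041/0.0158 ≈ −2.6, and 12% gives ln(0.88)/0.0158 = −0.128/0.0158 ≈ −8.1. Doubling the assumed SD halves both, to about −1.3 and −4.0. These values show only that a large sample detects small drifts. They do not estimate the bias in this study.

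**The case against.** **Cortisol is not a main outcome.** This stands. Neither Aim nor Outcomes names cortisol or an intervention effect, and the power statement concerns other variables. A reader might infer that a primary conclusion is at risk; the documents do not support that.

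**The Background also describes a sound use.** It speaks of cortisol reactivity to stressful experiences and of identifying children with higher responses. For comparing or ranking children, a time-of-day change common to all largely cancels, leaving differences in sampling time or slope. This stands, and it is the use the fix builds on. It does not justify the sentence that promises a benefit of physical activity.

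**No paired test is planned.** Also true. Statistical Analysis lists descriptive statistics, chi-square tests and multiple linear regression. A reader might infer from the table above that a false reduction in cortisol is nearly certain to be reported. That would need a paired mean-change analysis, a drift and a variance, none of which the documents give. That cortisol falls over the morning is itself not stated in the article.

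**The article is condensed.** Sampling clock times may well be recorded, so their absence from the text is no fault. But the full protocol or an analysis plan cannot supply a comparison that the described design lacks, and the wording appears in both Background and Methods.

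**Conclusion.** The point holds as a mismatch between a stated causal purpose and a design that cannot deliver it. It rests on the text alone: one acute maximal bout, samples before and after, no resting comparison described, and an observational label. It assumes only that the article omits no resting condition.

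The mean pre/post change should not be interpreted as an effect of physical activity, in either direction. The size of any bias is unknown, and the calculations are illustrative. The component is secondary, so this should be corrected but does not threaten the main analyses.

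**What to change.** - In the Background and in Salivary Sampling and Analysis, replace the intervention and benefit wording with a standardised exercise challenge. State that the mean pre/post change is descriptive and will not be interpreted as an effect of physical activity.
- Put the physical-activity question as an association between children: regress post-run cortisol on habitual accelerometer activity (already collected), adjusted for the pre-run value and for sampling clock times where recorded.
- Show this with and without adjustment for stages completed, as a sensitivity analysis. Adjustment handles unequal exercise dose but may also remove part of the fitness pathway of interest.
- Use the pre-8 am sample descriptively or as a covariate, not as a substitute control.

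The cost is rewording and one specified regression, with no extra saliva sample. The causal claim is given up. Clock-time adjustment is possible only where times were recorded; the legend to Figure 2 refers to sample collection in the past tense, so missing times may not be recoverable.

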## Methods

This study protocol followed the Standard Protocol Items: Recommendations for Interventional Trials guidelines (33). This protocol paper reports on the baseline and proposed follow-up procedures of the ExAMIN Youth SA study.

### Aim

The aim of this paper is to provide the protocol of the ExAMIN Youth SA study. The ExAMIN Youth SA study aims to determine the prevalence of childhood hypertension and obesity as clinical conditions in South Africa, with large artery stiffness and retinal microvascular diameters as primary contributors. We further aim to investigate the risk factors and mediators of both early vascular aging (arterial stiffness and retinal microvasculature) and the clinical conditions including physical inactivity, unhealthy diet, life stress and biomarkers.

### Outcomes

The study has the following outcomes based on primary school children in the North West province of South Africa:

To evaluate obesity and hypertension prevalence along with its determinants motor skills and physical fitness/activity, intake from food groups, and psychosocial behaviors.To assess the association of body mass index and blood pressure with central pulse wave velocity and retinal vessel diameters in South African children.To identify whether the associations of arterial modulation with physical fitness/activity, intake from food groups, and psychosocial behaviors are dependent on ethnicity.

### Study Design

The ExAMIN Youth SA study is an analytical, multidisciplinary, observational cohort study, designed to investigate the interplay between body composition, dietary intake, physical fitness, and physical activity, psychosocial stress, cardiovascular function as well as urinary and salivary biomarkers in 1,065 children (age 5–9 years) attending public primary schools in the North West province, South Africa. The study will obtain unique high-quality data at baseline and will expand the investigations after a 4-year follow-up period to identify exposures and early vascular changes that may contribute to cardiovascular disease development in children. An outline of the study design and procedures during the baseline phases are illustrated in Figure 1.

**Figure 1 F1:**
[figure not shown]
Flow diagram of the three phases of the baseline study population and data collection. **(A)** The pre-screening phase including the planning, organization, permission and recruitment; **(B)** The screening phase which involved participant assent and consent, and baseline data collection; and **(C)** The post-screening phase comprises of a multifaceted feedback process and data analysis.

### Setting of the Study

The study sites where data collection is performed are located within the [name] district in two of the southern municipal areas namely JB Marks (Potchefstroom) and Matlosana (Klerksdorp) (Figure 2). The majority of the population in these areas consist of black (82%), with the remainder comprising of 14% white, 4% mixed-race, and 1% Indian, as reported on wazimap.co.za (accessed on 16 August 2019). All the data collection procedures are conducted in a school-based setting with the endorsement and support of the District Director's office of the Department of Education.

**Figure 2 F2:**
[figure not shown]
Data and sample collection for the ExAMIN Youth SA study took place in Potchefstroom and surrounding areas as well as in Klerksdorp, both located in the Southern district of the North-West province of South Africa. The outline of the South African map was purchased from yourfreetemplates.com with the Creative Commons' license, which is Attribution-NoDerivatives 4.0 International (CC BY-ND 4.0).

### Eligibility Criteria

Children between the ages of 5 and 9 years (both sexes and all ethnicities in the geographical region of investigation) are invited to participate voluntarily and with parental permission. No *exclusion criteria* are applied; however, children will be excluded if no informed consent were obtained.

